## Abstract

**Background:**

Amblyopia is a common developmental disorder with reduced visual acuity and impairment in binocular functions. Patching the fellow eye, as the gold standard therapy in amblyopia, sometimes fails to achieve satisfactory outcomes because of poor adherence or delayed intervention. Recently, dichoptic/binocular digital therapy in amblyopia has been developed, but no evidence-based binocular treatments with superiority are available. Based on our previous study findings in neural deficits of unilateral amblyopia, we develop a paradigm of pathway-specific visual training using augmented-reality techniques, in which functions of the parvocellular pathway in the amblyopic eye are selectively pushed under binocular viewing. The aim of this trial is to assess the efficacy and safety of this innovative binocular, home-based treatment for children and adults with unilateral amblyopia. We hypothesize that augmented-reality pathway-specific binocular training will significantly improve visual functions compared with traditional patching.

**Methods:**

This is a superiority, multi-center, randomized, controlled trial involving 114 patients, aged between 5 and 55 years, with a diagnosis of unilateral amblyopia. Participants will be randomized 1:1 to either binocular training or patching, and will receive home-based treatment for 2 hours per day over a 13-week period. Their visual functions will be assessed at baseline, mid-treatment (week 2, week 4, week 9), and the end of treatment (week 13). The primary outcome is the change in best-corrected visual acuity at distance in the amblyopic eye from baseline to 13 weeks after treatment. Secondary outcomes include contrast sensitivity, near and far stereoacuity, interocular suppression, treatment adherence, and the incidence of adverse events at each visit.

**Discussion:**

This study is the first multi-center randomized controlled trial investigating a home-based augmented-reality binocular therapy targeting neural deficits in children and adults with unilateral amblyopia. We expect that the trial will generate findings that can provide an evidence-based basis for the efficacy and safety of this innovative approach to amblyopia treatment.

**Trial registration:**

ClinicalTrials.gov identifier: NCT06498206. Registered on July 12, 2024.

**Supplementary Information:**

The online version contains supplementary material available at 10.1186/s13063-025-08927-2.

## Administrative information

Note: the numbers in curly brackets in this protocol refer to SPIRIT checklist item numbers. The order of the items has been modified to group similar items (see http://www.equator-network.org/reporting-guidelines/spirit-2013-statement-defining-standard-protocol-items-for-clinical-trials/).

## Introduction

### Background and rationale {6a}

Amblyopia is a visual impairment with reduced vision and binocular dysfunctions due to abnormal binocular interaction and/or visual deprivation during the critical period of visual development, without any apparent organic lesion in the visual system. A meta-analysis showed the prevalence of amblyopia was estimated at 1.44% in the global population, and the highest prevalence was found in participants over 20 years old, which was 3.29% [1]. Amblyopic individuals experience a broad range of visual deficits besides reduced visual acuity, such as reduced contrast sensitivity, fixation instability, abnormal binocularity, spatial uncertainty, and impaired reading abilities [2–6]. Amblyopia is an important public health problem because of its prevalence in children, and the visual impairment as well as psychosocial issues from amblyopia can have a lifelong and profound impact on life quality if it is not treated effectively.

Patching the fellow eye (FE) is the gold standard for the treatment in amblyopic children, requiring patients to regularly wear an eye patch over the non-affected eye. It works by inhibiting the use of the FE, thereby forcing the use of the amblyopic eye (AE) to alleviate the suppression from the FE and improve the visual ability of the AE. However, this traditional method often leads to poor patient adherence due to its impact on daily life and self-esteem, resulting in less-than-ideal therapeutic outcomes and missed optimal treatment opportunities. Meanwhile, traditional patching for amblyopia has a high recurrence rate after a recovery of visual acuity [7, 8] and is mostly aimed at children under the age of about 7 [9]. For older children and adults, traditional patching always achieves limited effect [10], and there is a general belief that they have missed the critical period for visual recovery [9]. However, new therapies have emerged to find the way to address the drawbacks of traditional therapies, such as perceptual learning [11], binocular video games [12], and transcranial magnetic stimulation [13]. These methods also challenge the previous notion that amblyopia cannot be treated after the end of the critical period.

Contrary to the traditional view of "monocular amblyopia", studies in recent decades have revealed that amblyopia is a "binocular disorder", in which the stronger the inhibition of the AE from the FE, the greater the impairment in binocular functions [14]. Based on this new understanding, investigators have discovered binocular/dichoptic therapies with the hypothesis that rebalancing the inhibitory signals between the two eyes can minimize the suppression of the cortical input in the AE and thus promote the brain to learn to "see" through the AE [15]. Unlike previous monocular training, binocular visual training requires the simultaneous use of both eyes but different visual stimuli to each eye, not only to improve monocular vision of the AE but also to enhance the binocular functions, which should theoretically be a priority over the traditional patching [14]. Binocular/dichoptic training paradigms with reduced contrast in the FE's image and/or binocularly complementary images have been reported, aimed at rebalancing binocular inputs and enhancing binocular sensory fusion [15–17]. However, existing binocular training methods have some barriers to success, including unclear neural mechanisms, repeated visual stimuli or limited visual content, occupation of daily study or work time, and very little effect in older children and adults. So far, there is no evidence-based binocular treatment with superiority compared to patching available.

In this trial, we propose an innovative dichoptic training paradigm using the augmented reality (AR) technique [18], and compare the therapeutic outcomes between traditional patching and AR push-pull binocular training with randomized controlled design. This binocular training method has two major innovation points. Firstly, we design the training paradigm based on neural deficits we previously found. Using high-resolution fMRI technique, we found that stimuli presented to the AE shows selectively reduced response in the parvocellular (P) layers of the lateral geniculate nucleus and weaker effective connectivity to the early visual cortex V1 compared to magnocellular (M) layers [19]. Moreover, imbalanced binocular suppression and weakened binocular integration in the superficial layers of V1 using submillimeter 7 T fMRI, coexisting with attenuated and delayed monocular processing in V1 layers receiving thalamic input in human amblyopia [20]. These precise neural deficits help us to develop more targeted and effective treatments for amblyopia. Therefore, we combine the M-P pathways push-pull in the AE to selectively strengthen the P pathway in the AE, with the interocular P-P pathways push-pull to selectively strengthen the AE under binocular viewing condition. Secondly, we use augmented-reality technique and dichoptic head-mounted displays to achieve environment interactivity and free choice of visual content when training. AR technology processes the scenes in the real surrounding world in real time, extending or augmenting the reality by adding images, sounds, videos or other virtual details, with the virtual environment and the real environment coexisting and interactive, which enables participants to interact with the surrounding environment while performing diverse visual tasks, and also makes long-term training possible.

Our preliminary study with a prospective cohort ([name] et al., unpublished data) found innovative AR push-pull binocular training method showed effectiveness and safety in adults with unilateral amblyopia. The effective proportion was 60% (15/25) after treatment for 3 months, 2 hours per day, with effectiveness defined as improvement of at least 2 logMAR lines in best-corrected visual acuity (BCVA) at distance in the AE. Since the treatment response is believed age dependant in amlyopia, this method may bring benefits to patients with unilateral amblyopia including children and adults, which is a promising alternative in patients with treatment-resistant amblyopia or with poor adherence to patching. Therefore, in this multicenter, randomized controlled clinical trial, we evaluate the efficacy and safety of this AR training treatment compared with traditional patching in children and adults with unilateral amblyopia, and provide evidence for its further clinical application.

### Objectives {7}

The objective of this clinical trial is to evaluate the efficacy and safety of the AR binocular treatment we developed. The primary objective is to compare the total effective proportion, defined as the proportion of patients with improvement of BCVA at distance in the AE no less than 0.2 logMAR, after 13 weeks of AR binocular training with that of traditional patching in patients with unilateral amblyopia. The secondary objectives of this study are (1) to compare the improvement in the visual functions at each follow-up visit between the two groups, including habitual-corrected visual acuity at distance, contrast sensitivity, near and far stereoacuity, and interocular suppression, (2) to compare the treatment adherence and adverse events between the two groups.

### Trial design {8}

This study is a multicenter, superiority, parallel randomized controlled trial using a 1:1 parallel control design. A total of 114 patients with unilateral amblyopia will be enrolled in 4 centers (Shanghai Eye & ENT Hospital of Fudan University, First Affiliated Hospital of Fujian Medical University, Shanghai Tongren Hospital of Shanghai Jiao Tong University School of Medicine, and Jiangsu Provincial People's Hospital) in China. All patients are stratified and randomly assigned to the intervention (AR pathway-specific binocular training) group and the positive control (patching) group according to age. Based on full-time refractive correction, patients receive AR binocular training or patching therapy 2 hours per day, 7 days per week for 13 weeks for a total of 182 hours. The consistency in treatment exposure time between interventions strengthens the validity of direct comparisons in efficacy and safety, controlling for potential confounding effects of dosage variations. Patients will be followed up at 2, 4, 9, and 13 weeks (± 3 days) after enrollment, during which examiners are masked to treatment group assignments, whereas patients and study coordinators who administered interventions were not masked. The primary outcome is the change of BCVA at distance in the AE at 13 weeks measured by the electronic Early Treatment Diabetic Retinopathy Study (ETDRS) chart with Tumbling E target.

## Methods: participants, interventions, and outcomes

### Study setting {9}

Initiated and led by Shanghai Eye & ENT Hospital of Fudan University, this study was launched in August 2024 and planned to enroll 114 patients with unilateral amblyopia from 4 centers (Shanghai Eye & ENT Hospital of Fudan University, First Affiliated Hospital of Fujian Medical University, Shanghai Tongren Hospital of Shanghai Jiao Tong University School of Medicine, Jiangsu Provincial People's Hospital) in China over 12 months (anticipated recruiment duration). Each patient and/or the guardian was required to sign an informed consent prior to enrollment. Each center will apply to the Ethics Committee for ethical review.

### Eligibility criteria {10}

This study planned to enroll patients in the outpatient of each participating center. Patients were screened and enrolled under quiet conditions in the outpatient, and those who were younger than 18 years old should be accompanied by a guardian.

#### Inclusion criteria

Patients must meet all of the following criteria to be enrolled in this trial:

Age: 5 to 55 years (inclusive);BCVA: Interocular difference of 0.2 logMAR or more, with BCVA in the AE < 1.0 logMAR and BCVA in the better eye within age-normal limits;Risk factors of amblyopia, such as anisometropia, strabismus, deprivation;Patients with deprivation amblyopia must have undergone surgical interventions to address the underlying structural causes of deprivation (e.g., cataract extraction with intraocular lens implantation, ptosis correction surgery, etc.);Optical refractive correction in full time, if needed, for no less than 3 months;Orthotropia (orthotropia with refractive correction or after strabismus surgery) or intermittent exotropia with good fusional control;No ongoing or other planned amblyopia treatment (except spectacles).

#### Exclusion criteria

Patients could not be included in this trial if they met any of the following criteria:Ongoing structural pathology in the visual system (e.g., ptosis, media opacity, nystagmus, paracentral fixation, optic nerve diseases like glaucoma, retinal diseases, cortical visual impairment, etc.);History of ocular surgery that affects vision (except surgery to remove the causative factors of amblyopia, such as strabismus surgery and congenital cataract surgery);Significant systemic disorders (e.g., epilepsy, cognitive impairment);Implantable electronic device;Ongoing or planned use of medications that may affect vision (except dilating eye drops e.g. atropine used for optometry examinations);Those who have diplopia and can not achieve binocular fusion when using the AR binocular training devices;Pregnant or breastfeeding women, or women planning to become pregnant.

### Who will take informed consent? {26a}

The target population was patients with unilateral amblyopia, who come to the centers and meet the eligibility criteria. For patients meeting the eligibility criteria, the investigator must provide them with the details of this clinical trial prior to enrollment, including the contents and purpose of the trial, intended efficacy, possible adverse events, and corresponding countermeasures. The patients can only be enrolled when they have fully understood this trial and signed the informed consent form. For child participants aged 5 to < 8, parents or guardians in accordance with the law need to provide written informed consent for participation. For child participants aged 8 to < 18, they should also give oral informed consent besides written informed consent signed by parents or guardians. For adult participants, they need to sign the written informed consent form by themselves. The informed consent form is developed in accordance with the Declaration of Helsinki, which will be in duplicate and jointly signed by the investigator and the participant and/or his or her guardian, each copy for each party. Participants can withdraw from the study any time they want with no effect on their subsequent care. Informed consent has already been evaluated by the Ethics Committee of Eye & ENT Hospital of Fudan University (Ethical code: [2024]No.2024114).

### Additional consent provisions for collection and use of participant data and biological specimens {26b}

N/a.

Explanation: all patient information, biological samples, and imaging data required for the exploratory endpoints of this study were included in the formal informed consent and were fully informed by the investigators at the time of enrollment.

## Interventions

### Explanation for the choice of comparators {6b}

A total of 114 patients were randomly divided into the following two groups according to age (≥ 18 years old, < 18 years old): (1) AR pathway-specific binocular training group and (2) patching group.

### Intervention description {11a}

#### AR pathway-specific binocular training system

We develop AR binocular training for amblyopia treatment, including original hardware and software. Environmental images are captured through the high-speed and high-resolution camera, which are processed by the graphic process unit of a laptop and displayed on the head-mounted dichoptic displays in real time, allowing the patients to interact with the surrounding environment during the visual training. Using the AR technique, images were processed differently and presented dichoptically to the AE and the FE simultaneously, the same in content but different in contrast, spatial frequency, and temporal frequency (Fig. 1). To selectively enhance the P pathway, which is notably impaired in amblyopia, the low spatial frequency components of visual input to the AE are phase-scrambled into fast-flickering noise with reduced contrast, while the high SF details remain intact with full contrast, to achieve push-pull in monocular P-M pathways in the AE (Video S1). Meanwhile, the high-frequency components of visual input to the FE are processed into slow-flickering noise with a low signal-to-noise ratio (Video S2), to achieve push-pull in interocular P-P pathways between the AE and the FE. More details about the design of the AR pathway-specific binocular training paradigm have been reported in our study published recently [18].

**Fig. 1 Fig1:**
[figure not shown]
Schematic of AR pathway-specific binocular training. **a** Dichoptic images processing in the amblyopic eye and fellow eye. **b** In this demo, the participant was playing a video game while wearing AR glasses. Right panels show the processed images presented to the amblyopic eye and fellow eye

The AR binocular training system has passed the test conducted by Centre Testing International Group Co., Ltd., a leading third-party testing and certification organization in China, accredited with China Metrology Accreditation and China National Accreditation Service for Conformity Assessment certifications. Therefore, this investigational medical device has been certified to meet the prerequisites for conducting a clinical trial. This Class II innovative medical device has been accepted into the Expedited Review Program for Innovative Medical Devices by Zhejiang Medical Device Evaluation Center. According to the national regulations, ethical requirements, and the characteristics of the investigational product, the efficacy and safety of the hardware and software involved in this treatment will be verified.

#### Intervention group

In the intervention group, participants will be required to have AR pathway-specific binocular training at home for 2 hours per day, 7 days per week for 13 weeks, wearing head-mounted dichoptic displays. The backend of the training system will record participants' daily training duration for adherence analysis.

#### Positive control group

In the control group, participants will be required to patch the fellow eye at home for 2 hours per day, 7 days per week for 13 weeks. The daily actual patching duration should be recorded by the participants or their guardians in the diary cards provided.

Participants in both groups are instructed to engage in the same visual tasks during treatment sessions, such as watching video, reading e-books/paper books and comics. For the AR training group, these contents are projected onto the AR glasses' displays, whereas patients in the patching group view them directly. All centers use fabric patches (non-adhesive, wrapping the spectacle lens) to ensure consistent light-blocking efficacy.

### Criteria for discontinuing or modifying allocated interventions {11b}

#### Withdrawal criteria and procedure

Withdrawal at the investigator's discretion:under circumstances where the investigator decides to withdraw the case from the trial since the patient enrolled is not suitable for further study during the trial, mainly including:i.Serious adverse event or intolerable adverse event during the trial;ii.Comorbidities, complications, or significant physiological changes during the trial;Self-withdrawal of the patient from the trial, including:i.Unwillingness to continue the clinical trial;ii.Loss to follow-up.

The investigators must make a detailed evaluation of the patient withdrawn from the trial due to unexpected adverse events, take active treatment measures, document the entire process in detail, and make frequent follow-ups until the condition is under control. Patients withdrawn from the trial due to personal reasons unrelated to the trial can receive clinical routine treatment, and the routine treatment of patients after the withdrawal will not be affected by this study.This study does not involve intervention modifications. All data of participants randomized are preserved in the EDC system to ensure analytic completeness under the intention-to-treat (ITT) principle, while protocol deviations like non-adherence are documented and analyzed separately.

### Strategies to improve adherence to interventions {11c}

Investigators can verify the treatment adherence of patients by checking their daily training records through the backend of the training system in the AR binocular training group or their daily record cards in the patching group. Training or patching for 2 hours per day will be considered as having completed the treatment for that day, with less than 2 hours considered not reaching an effective dose. The investigator should inform the patient to try to avoid an interruption in training; if there is an interruption, the backend of the system stops the timing, but the time period of training in the same day will be accumulated. During the training process, the system will record the training duration and completion status. If patients do not complete the effective dose for two consecutive days, the researcher will remind them by phone. The abnormal training data detected in the backend for two consecutive days will be verified by phone and recorded truthfully.

The adherence will be calculated based on the actual number of days the treatment of 2 hours completed at each follow-up visit. In order to ensure the adherence to interventions as well as correct and effective training, the following methods are adopted to guide and monitor patients' daily treatment: (1) assistance from doctors and trainers: a guide video is sent to the patients to help them to master the entire operation procedure and to inform important cautions. If patients have any questions about the treatment process, they can contact the doctors or trainers to solve problems through online communication; (2) family assistance: for patients aged under 18, the doctor and trainer will train their family to understand the operation at the baseline visit; (3) incentive measures: for each enrolled patient, we promise to give one year of AR binocular training device use right after the end of the study to encourage them to actively complete the trial.

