#### Secondary outcomes

Secondary outcomes included the mean change from baseline to week 13 in the habitual-corrected visual acuity at distance in the AE, the contrast sensitivity in each eye, the stereoacuity at near and distance, the interocular suppression measured by worth-4 dot at near and distance, and the interocular suppression measured by Bagolini striated lens at near and distance, the treatment adherence and safety reports. Additional outcomes included all the measures at week 2, 4, and 9 for the analysis of within-person changes over time.

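### Adherence is to be compared between arms, but it comes from a device log in one arm and an unmasked diary in the other, so a null result or a patching advantage could be a measurement artefact

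*Protocol article*

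**What the plan says.** All references are to the protocol article.

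- **Purpose.** Objectives {7} sets as a secondary aim "to compare the treatment adherence and adverse events between the two groups". Secondary outcomes lists "the treatment adherence and safety reports".
- **AR arm.** Under Intervention group, the system backend records "daily training duration for adherence analysis".
- **Patching arm.** Under Positive control group: "The daily actual patching duration should be recorded by the participants or their guardians in the diary cards provided". Procedure for unblinding {17b} states that participants are not blinded.
- **Source used.** Strategies to improve adherence {11c} describes the investigators' check as "checking their daily training records through the backend of the training system in the AR binocular training group or their daily record cards in the" (the control arm is named next).
- **What counts as a day.** The same section treats 2 hours as a completed day in either arm, "with less than 2 hours considered not reaching an effective dose". It continues: "The adherence will be calculated based on the actual number of days the treatment of 2 hours completed at each follow-up visit".
- **AR timer.** "if there is an interruption, the backend of the system stops the timing", but minutes trained on the same day are added up.
- **Metric.** Baseline and follow-up assessments gives one formula for both arms, completed days over scheduled days, and four grades: excellent (76-100%), good (51-75%), fair (26-50%) and poor (25% or below).
- **Test.** Statistical methods {20a} prescribes t or Wilcoxon tests for quantitative variables and chi-square or exact tests for categorical ones. It names no separate method for adherence.

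**The concern.** The two arms share a formula, a cut and a grading scale, but not an instrument. A timer measures to the minute. A person filling in a card may round, or may record a short day as a full one. With an all-or-nothing cut at 120 minutes, a 115-minute day scores 0 in the log and 1 on a card that rounds it to 2 hours. A between-arm test run as written therefore compares measuring methods together with behaviour. The article describes no instrument common to both arms, no objective measure of patch wear, no check of the diary and no caveat on the comparison.

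This is not a detail left to a statistical analysis plan. The data source for each arm is already fixed, and no later analysis can recover readings from an instrument that one arm did not use.

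At stake is the adherence conclusion. The Background gives poor adherence as a weakness of patching, and the Discussion expects better adherence with AR training. The probable bias runs against that expectation.

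**Working it through.** **Plan's own figures.** Scheduled days are 7 × 13 = 91 and scheduled hours 2 × 91 = 182, which agrees with Trial design {8}. Each arm has 33 + 24 = 57 participants. The article gives no expected adherence, no distribution of daily time and no diary accuracy, so everything below is illustration under stated assumptions.

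**Rounding.** Assume that daily minutes X are normal with the same mean m and SD s in both arms.

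- The log counts a day when X ≥ 120.
- A diary rounded to the nearest 15 minutes counts it when X ≥ 112.5.
- A diary rounded to the nearest 30 minutes counts it when X ≥ 105.
- Share of days counted = 1 − Φ((cut − m)/s).

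With s = 20:

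| Mean | Log | Diary, 15 min | Diary, 30 min | Gap (points) |
|---|---|---|---|---|
| 115 | 1 − Φ(0.25) = 40.1% | 1 − Φ(−0.125) = 55.0% | 1 − Φ(−0.5) = 69.1% | 15 to 29 |
| 120 | 50.0% | 64.6% | 77.3% | 15 to 27 |
| 130 | 69.1% | 80.9% | 89.4% | 12 to 20 |
| 150 | 1 − Φ(−1.5) = 93.3% | 1 − Φ(−1.875) = 97.0% | 1 − Φ(−2.25) = 98.8% | about 4 to 6 |

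At mean 115 identical behaviour is graded fair by log and good by diary. At mean 150 all three are excellent. Over means 110 to 130, SDs 10 to 30 and rounding to 10, 15 or 30 minutes, the gap runs from 6 points (mean 130, SD 30, 10 minutes: 69.1 − 63.1) to 53 points (mean 110, SD 10, 30 minutes: 69.1 − 15.9).

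**Over-reporting.** If true adherence is a and a share f of missed days is written down as completed, the diary exceeds the truth by f(1 − a). For a = 80% and f = 10% this is 0.10 × 0.20 = 2 points. For a = 50% and f = 50% it is 0.50 × 0.50 = 25 points.

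**Would such a gap be declared significant?** Assume 57 per arm, equal true adherence, a two-sided 5% comparison of means and a between-participant SD of adherence of 20 to 30 points.

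| Pure measurement gap | Probability of p < 0.05 |
|---|---|
| 5 points | 0.14 to 0.27 |
| 10 points | 0.43 to 0.76 |
| 15 points | 0.76 to 0.98 |

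All exceed the nominal 0.05.

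**The case against.** Several points on the other side stand.

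- **Direction.** A reader might infer that the comparison cannot be interpreted at all. The mechanism described runs mainly one way: it raises patching. An AR advantage seen despite it would be conservative, and description within each arm remains usable.
- **Interruptions.** A reader might infer that the AR timer penalises broken sessions. It does not, because minutes accumulate within the day.
- **The cut.** The 2-hour rule is the same in both arms. It does not create the asymmetry; it magnifies a difference in precision. Minutes are recorded in both arms, so a minutes-based measure needs no new data.
- **Size.** The gap of 15 to 29 points depends on placing the mean just below the cut. If days are mostly either full or missed, rounding adds almost nothing.
- **Calibration.** It is tempting to give AR participants a diary and use their log to show how far patching diaries over-report. AR participants know that they are logged, since the site phones them about shortfalls or abnormal backend data. Their diaries may be more accurate than patching diaries.
- **Reach.** The primary outcome is analysed by randomization regardless of adherence ({20c}), and the per-protocol definition names no adherence threshold.

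These points limit the finding but do not remove it. Nothing in the article makes the two sources comparable, and a null result or a patching advantage would stay ambiguous.

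**Conclusion.** The concern holds in limited form. As planned, the between-arm adherence comparison mixes measuring method with behaviour. The likely bias favours patching, so an AR advantage would probably be understated, while a null result or a patching advantage could be artefact. The direction is probable rather than proven: it assumes that diaries err upwards more than the log does, and the log itself times device use, not attention.

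The size is unknown. The figures of about 4 to 6 points (mean 150) and 15 to 29 points (mean 115) assume normal daily minutes, SD 20, identical behaviour and diary rounding to 15 or 30 minutes. They show the range, not an estimate.

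A reader might also infer that the efficacy result is compromised. The article does not support that, because the primary analysis does not use adherence. The point is worth acting on because the change is cheap and alters what the trial may claim about adherence.

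**What to change.** 1. Report adherence descriptively by arm, naming the source each time (device log for AR, diary for patching). State that no confirmatory between-arm conclusion is drawn from log against diary, and reword the secondary objective to match.
2. Beside the 2-hour-day measure, report recorded minutes over scheduled minutes in each arm. The data are already collected. This removes the all-or-nothing cut from the summary but not the difference in source.
3. Optionally, give the same diary card to AR participants still to be enrolled and present diary against diary as a sensitivity comparison. State that AR participants know they are logged, so the comparison may still understate over-reporting in the patching arm.

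**Cost.** Items 1 and 2 are text and a small analysis, and remain possible whatever the enrolment status. The price is a weaker adherence claim. Item 3 adds a small diary burden, may need approval as an amendment ({25}) and yields no AR diary data for those already enrolled. Trial status reports 43 of 114 enrolled, so at that date 114 − 43 = 71 remained across both arms; fewer may remain now. The prescribed treatment is unchanged.
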